## Statistical analysis

All the variables will be descriptively analyzed by arm and visit (mean, median, standard deviation, minimum and maximum for continuous variables, and frequency distribution for categorical variables). Categorical variables referring to a physical examination, vital signs and laboratory abnormalities will also be analyzed with shift tables (baseline vs. final visit). All analyses will be carried out in details in the respective Statistical Analysis Plan (SAP), which will be finalized in Version 1.0 before the database freezing.

Version 2.0 of the SAP will be prepared after the Data Review Meeting (in which the protocol violations will be evaluated) and will include the list of the patients belonging to the defined populations and the randomization list.

A descriptive analysis of demographic data and baseline characteristics will be carried out to verify the balance of the two arms at the study entry.

The delta ST-segment elevation by intracoronary ECG during two-step sequential coronary balloon inflation in the culprit vessel will be compared between the ticagrelor and clopidogrel arms by using two-way ANOVA (2 × 2). Missing data in the primary analysis will be handled by simple imputations. An interim efficacy analyses will be conducted after the accrual of two-third of therandomized patients have been reached.

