## Materials/Methods

### TAPER-S trial design

This study is a prospective, randomized, blinded, end-point trial that will enroll patients with multivessel CAD requiring scheduled treatment of a second lesion located in a nonculprit vessel. The typical patient will be a patient with purely stable CAD and a scheduled, FFR-guided PCI of any vessel. Patient presenting initially with an ACS, with an intermediate coronary lesion (40–80% in severity, where functional evaluation of the stenosis with FFR must be used based on clinical situation) in a nonculprit coronary artery, for whom a delayed, FFR-guided strategy is chosen, may also be included in the study. In these patients, recovery of the microvascular function requires that at least 1 month has elapsed before re-evaluation of the culprit lesion, as FFR in the acute phase is known to be unreliable [31]. Screening/randomization will take place 1 to 3 days before the index procedure. Randomization will be blocked within each study site, which will allow an even balance of patients to be randomized to either drug at each recruiting center. Patients with FFR > 0.80 (no functionally significant stenosis) will be excluded from the study (Figs. 1 and 2). The study will be conducted in Italy, involving A. Gemelli Polyclinic of the Catholic University of the Sacred Heart in Rome and Grosseto Hospital (Ospedale della Misericordia Grosetto) in Grosetto, Italy.

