### Sample size

This is an exploratory and pilot study, aimed at evaluating the off-target effects of ticagrelor on ischemic preconditioning. A sample size of 40–60 patients is, in general, considered appropriate for a pilot study and should provide important insights for the planning of a future larger study and for estimating confidence intervals [32]. Per our design, by assuming an absolute difference (delta) of 4 mm in the change of ST-segment shift from the first to the second balloon inflation between the two compared groups, a magnitude similar (albeit reversed) to the effect observed by Niccoli et al. in a study demonstrating the negative preconditioning effect of ethanol [33], we can infer that 30 patients per group will be required to provide an 80% power to detect a statistically significant difference between groups at a significance level set at *p* < 0.05. The standard deviation (SD) of the primary endpoint is expected to be approximately 5 to 4 mm in each treatment group. By enrolling one hundred patients, we also take into account those patients that will not require PCI after FFR evaluation (as observed in the FAME II trial) [34].

The main statistical analysis to be undertaken is a comparison of the primary endpoint (continuous variables) between the two groups of 30 patients each is a 2 × 2 analysis of variance (ANOVA) stratified by treatment group. The co-primary safety endpoint, which is a frequency value, will be analyzed using a Fisher’s exact test.

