### Randomization

Patients will be randomly assigned to **ARM A (clopidogrel)** or **ARM B (ticagrelor)** in a 1:1 ratio. The allocation to the assigned treatment arm will be known to the patients and to the Principal Investigator (PI) and/or his delegates.

The randomization will be performed at Visit 0. Randomization process will be performed printing 50 tags reporting the word *“Ticagrelor”* and 50 tags reporting the word *“Clopidogrel”* inserted into anonymous white letter envelopes; the envelopes will be mixed and then stacked up in random order, with the opening side toward the bottom of the pile, by the study monitor; the resulting random sequence of 100 envelopes will be consigned to the PI or his delegates, which are entrusted with their preservation and responsible for any adulteration. At visit 0 the PI or his delegates will open the first available envelope, proceeding from top to bottom of the pile. The already opened envelopes will be stored separately from the others and will be available to the study monitor on request.

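### The design section blocks randomisation by site, but neither description of the primary 2 × 2 ANOVA names site or its second factor; adding site is a small, nearly free gain

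*Protocol article*

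**What the plan says.** All references are to the Protocol article.

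- **TAPER-S trial design:** "Randomization will be blocked within each study site, which will allow an even balance of patients to be randomized to either drug at each recruiting" centre. The two sites are the Gemelli Polyclinic "in Rome and Grosseto Hospital". Site is the only factor the article ties to the allocation.
- **Randomization:** a different procedure. Fifty tags per drug go into plain envelopes, which are mixed into one pile; "the resulting random sequence of 100 envelopes will be consigned to the PI or his delegates", who open them from the top down. This section mentions neither blocks nor separate piles by site.
- **Sample size:** the main analysis of the primary endpoint "is a 2 × 2 analysis of variance (ANOVA) stratified by treatment group".
- **Statistical analysis:** the ST delta "will be compared between the ticagrelor and clopidogrel arms by using two-way ANOVA (2 × 2"). Details are deferred to an SAP that is not at hand.

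Neither account of the primary model mentions site, and neither identifies the second two-level factor.

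**The concern.** A factor that constrains the allocation normally belongs in the analysis. When the arms are balanced within each site, site differences cancel out of the treatment contrast. A model without site still leaves that variation in its residual. The reported standard error is then larger than the true one, the confidence interval is too wide, and the test rejects less often than 5% under the null.

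This has some relevance here because about 30 patients per arm will be analysed and the Sample size section gives estimation of confidence intervals for a later trial as one purpose of the pilot. A site effect on the delta is conceivable: operators measure the ST elevation, two ECG filter ranges are allowed, and the mix of post-ACS and stable patients may differ by centre. The document gives no figure for it.

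**Working it through.** **Inputs.** Effect: "by assuming an absolute difference (delta) of 4 mm in the change of ST-segment shift from the first to the second balloon inflation". Spread: "The standard deviation (SD) of the primary endpoint is expected to be approximately 5 to 4 mm in each treatment group". Thirty per arm, 80% power and p < 0.05 are from Sample size; two-sided testing is assumed. The step from 100 enrolled to 60 evaluable (10% drop-out, 30% negative FFR) is from the design section. Two quantities are assumptions: the share of delta variance explained by site (R²) and the share q of patients at the smaller site.

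**The plan's own figure.** n per arm = 2(1.960 + 0.842)² SD² / 4².
- SD 5: 2 × 7.85 × 25 / 16 = 24.5, so 25 (26 with the t distribution).
- SD 4: 2 × 7.85 × 16 / 16 = 15.7, so 16 (17 with t).

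The stated 30 does not reproduce; it would need an SD of about 5.4 to 5.5 mm. That is a separate matter and errs towards more power. With 30 per arm and SD 5, the standard error is 5√(2/30) = 1.29 mm and power by the noncentral t is 86.1%. At SD 4 it is 96.8%.

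**What R² means in mm.** Site difference D = SD × √(R² / (q(1 − q))). At SD 5:

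| R² | equal split (q = 0.5) | 80:20 split (q = 0.2) |
|---|---|---|
| 0.05 | 2.2 mm | 2.8 mm |
| 0.15 | 3.9 mm | 4.8 mm |
| 0.25 | 5.0 mm | 6.25 mm |

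So R² = 0.15 already needs a site difference in the delta about as large as the 4 mm assumed for treatment.

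**Exact balance within site.** The model without site overstates the standard error by a factor 1/√(1 − R²). For D = 2 mm at SD 5 this is 1.3% to 2.1% (q = 0.2 to 0.5). Power is 86.4–86.6% without site and 87.0–87.5% with it. For D = 4 mm it is 5.6% to 9.1%, and power is 87.4–88.1% against 89.5–91.4%.

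Blocking itself raises unadjusted power above 86.1%, so comparing site-adjusted power with 86.1% would overstate the gain. At R² = 0.15 the like-for-like comparison is 88.0% against 91.1%.

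**Allowing for losses.** About 40 of 100 patients leave after randomisation, so balance within site is only approximate among the 60 analysed. Simulated with site blocking, SD 5 and a 4 mm effect:

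| R² | unadjusted type I error | power gain from a site term |
|---|---|---|
| 0.05 | about 4.5% | about 1 point |
| 0.15 | about 4.0% | about 4 points |
| 0.25 | about 3.4% | about 6 points |

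**The two randomisation descriptions compared** (D = 4 mm, 60 of 100 analysed, q from 0.2 to 0.5):

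| | blocked by site | one pile of 100 |
|---|---|---|
| mean model SE without site | 1.29 | 1.29 |
| true SE of that estimate | 1.24–1.26 | 1.28–1.30 |
| type I error without site | about 4.1% | about 4.9% |
| power without site | 86.6–86.9% | about 86% |
| power with site | 89.0–91.2% | 89–91% |

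The overstated standard error appears only in the first column. The precision gain appears in both.

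**Cost if site explains nothing.** Residual degrees of freedom fall from 58 to 57 and power from 86.14% to 86.12%.

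**The case against.** The strongest objections are these.

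- *The absence of site is inferred from silence.* This stands. If the per-patient delta is the response, inflation number cannot also be a factor, so the second two-level factor is open, and with two sites it could even be site. If the model is arm by inflation, site is absent. A reader might infer that the plan rules site out; the text does not say so.
- *Covariates are commonly left to the SAP.* This is fair, and it limits how hard the point can be pressed. It does not remove it: the article names the primary method twice and a blocking factor once, and does not connect them.
- *The operational randomisation text has one unblocked pile.* This also stands. A reader might infer that the standard error is wrong whenever sites differ. Under the single pile the unadjusted test is valid, and only optional precision is lost.
- *The effect is small.* Agreed. The endpoint is a within-patient change, so a constant site shift in ST level cancels; only a site difference in the change itself matters. For site differences up to 2 mm the gain is about 1 point or less.

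**Conclusion.** The point holds in a limited form. Site is stated as the blocking factor in one section and is not named in either account of the primary model, whose second factor is undefined. If allocation is blocked by site and the ST delta differs by site, omitting site makes the analysis slightly conservative. If the single pile is used, it only gives up precision.

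The sizes rest on assumed site effects, two-sided 5% testing, SD 5 mm and 60 of 100 patients analysed. At SD 4 mm there is less to gain, since power starts at 96.8%.

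A reader might infer an underpowered trial, a biased estimate or a raised false-positive risk. None follows: unadjusted power stays above the stated 80% at both stated SDs, the treatment estimate is unbiased, and any error in the test is on the conservative side. This is an optional, nearly free improvement.

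**What to change.** 1. Reconcile the TAPER-S trial design and Randomization sections so that one allocation scheme is stated.
2. In Sample size and Statistical analysis, name the terms of the primary model and state that the response is the per-patient ST delta.
3. Include study site (two levels) as a fixed main effect. Report the site-adjusted treatment difference with its 95% confidence interval, and the unadjusted result as a sensitivity analysis.

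The cost is a few sentences, settled no later than SAP version 1.0, which is due before the database is frozen. Site is known for every patient, so no new data or patients are needed. The statistical cost is one degree of freedom, about 0.02 points of power if site explains nothing.

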### Study endpoints

#### Primary endpoint

The primary endpoint is the comparison of ticagrelor and clopidogrel for the delta (difference in mm) of the ST-segment elevation, as assessed by the intracoronary ECG during two-step sequential coronary balloon inflation in the index vessel.

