#### Ischemic preconditioning

During PCI, two sequential balloon inflations will be performed to measure preconditioning. Operators will measure the degree of ST-segment elevation by intracoronary ECG and by surface ECG during coronary balloon inflation.

Specifically, after passage of the guidewire through a target stenosis and then advancement of the balloon catheter across the stenosis, the intracoronary unipolar ECG from myocardium distal to the stenosis to be dilated will be obtained, connecting the proximal end of the guidewire as it exited from the balloon catheter. The unipolar intracoronary ECG will be filtered between 0.1 to 100 or 0.1 to 500 Hz and then displayed simultaneously with the standard surface leads being monitored. Surface and intracoronary ECGs will be recorded simultaneously and continuously during balloon inflation and deflation [43–45].

Moreover, angina score during coronary balloon inflation will be registered by using a Visual Analog Scale (VAS) on a scale of 0 (no pain) to 10 (most severe pain) [46]. For pharmacodynamic considerations, the Index PCI will be performed at 4 ± 1 h after ticagrelor or clopidogrel last dose.

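### The named primary test, a 2 × 2 ANOVA with no stated second factor, does not match an endpoint of one delta per patient compared between two arms

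*Protocol article*

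**What the plan says.** All references are to the protocol article.

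- **Primary endpoint:** "The primary endpoint is the comparison of ticagrelor and clopidogrel for the delta (difference in mm) of the ST-segment elevation". The section on ischemic preconditioning adds that "two sequential balloon inflations will be performed to measure preconditioning", so each patient gives two readings and one delta.
- **Sample size, assumptions:** a 4 mm difference "in the change of ST-segment shift from the first to the second balloon inflation between the two compared groups", an SD of 4 to 5 mm stated for the endpoint itself, 30 patients per group, 80% power and a 0.05 significance level.
- **Sample size, analysis:** the main analysis of the primary endpoint between the two groups "is a 2 × 2 analysis of variance (ANOVA) stratified by treatment group".
- **Statistical analysis:** the delta "will be compared between the ticagrelor and clopidogrel arms by using two-way ANOVA", with 2 × 2 in brackets. Detail is left to an SAP whose first version is due before the database is frozen. The same section plans an interim efficacy analysis at two-thirds accrual.

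**The concern.** The endpoint, the effect size and the SD all describe one number per patient compared between two arms. That is a single-factor comparison. A two-way 2 × 2 ANOVA needs a second two-level factor, and neither section names one.

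The omission matters because the primary effect depends on what that factor is. If it is a between-patient factor and delta is the response, the arm main effect answers the question. If it is inflation (first or second) and the raw ST readings are the response, only the arm × inflation interaction does; the arm main effect then compares average ST elevation, which is not the endpoint. The article does not choose.

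The stratification phrase adds to the difficulty. A stratifier is held fixed while something else is compared, but treatment is the thing being compared.

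At stake are the power and error rate of the primary test. Under some readings they are what the sample-size section intends; under one they are not.

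**Working it through.** **1. The plan's own figure.** Inputs from the Sample size section: difference 4 mm, SD 4 to 5 mm, 80% power, alpha 0.05 (two-sided assumed, as sidedness is not stated).

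n per group = 2 × (1.960 + 0.842)² × SD² / 4²

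- SD 5: 2 × 7.849 × 25 / 16 = 24.5, so 25 (26 with the t distribution).
- SD 4: 2 × 7.849 × 16 / 16 = 15.7, so 16 (17 with the t distribution).

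The stated 30 is not reproduced, but it errs on the large side. Exactly 80% power at 30 per group would imply an SD of about 5.5 mm. With 30 per group, a t-test on delta has 86% power at SD 5 and 97% at SD 4. This is the benchmark.

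**2. Readings of the 2 × 2.**

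| Reading | Response | Test of the endpoint | Validity |
|---|---|---|---|
| A. Arm × a between-patient factor (e.g. site or patient type) | delta | arm effect | valid; factor not named |
| B. Arm × inflation, with patient term | raw ST | interaction | identical to the t-test on delta |
| C. Arm × inflation, no patient term | raw ST | interaction | wrong standard error unless rho = 0 |

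**3. Size of the problem under reading C only.** Let rho be the correlation between a patient's two readings. The article does not give it, so 0 to 0.7 is an assumed range. With SD of delta fixed, the SD of a single reading is SD(delta) / √(2(1 − rho)).

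*Interaction.* The true standard error is SD(delta) × √(2/30), which is 1.291 at SD 5. The ANOVA's standard error is larger by a factor 1/√(1 − rho). With 116 residual df the critical value is 1.981, so

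- power ≈ Φ(4 / 1.291 − 1.981 / √(1 − rho)) at SD 5;
- type I error ≈ 2 × [1 − Φ(1.981 / √(1 − rho))].

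Example, SD 5 and rho 0.5: 3.098 − 2.801 = 0.297, and Φ(0.297) = 61.7%.

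*Arm main effect* (not the endpoint). The ANOVA's standard error is too small by a factor √(1 + rho), so type I error ≈ 2 × [1 − Φ(1.981 / √(1 + rho))]. At rho 0.5: 1.981 / 1.225 = 1.617, giving 10.6%.

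Formula and simulation (20,000 trials per setting, 30 per arm):

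| rho | Interaction power, SD 5: formula / simulated | Interaction power, SD 4: formula / simulated | Interaction type I error, simulated | Arm main effect type I error, simulated |
|---|---|---|---|---|
| 0 | 86.8% / 86.5% | 97.1% / 96.8% | 5.0% | 4.9% |
| 0.3 | 76.8% / 76.3% | 93.4% / 93.2% | 2.0% | 8.5% |
| 0.5 | 61.7% / 61.4% | 85.8% / 85.1% | 0.6% | 10.8% |
| 0.7 | 30.2% / 30.7% | 60.1% / 59.7% | 0.05% | 13.3% |

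In the same simulations the t-test on delta kept a type I error of 4.8% to 4.9% and its power did not change with rho (86% at SD 5, 97% at SD 4).

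**The case against.** The strongest reply is that the Statistical analysis sentence makes delta the response and compares it between arms. Three stronger conclusions that a reader might draw therefore lack support.

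- *That the analysis as written ignores the pairing of the two inflations.* Taking a delta already uses the pairing, and nothing says raw readings enter as independent observations.
- *That a 2 × 2 can only mean raw readings.* The article has two-level between-patient factors: two sites (trial design section) and two patient types (study population section). Crossing either with arm, with delta as response, is a valid layout.
- *That stratifying by treatment means separate within-arm tests.* The same sentence describes a comparison between the two groups, and the Statistical analysis section also compares the arms.

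It can also be said that error structure and covariates normally belong in the SAP, which is not shown, and that this is a self-described exploratory pilot. That stands too: the lack of a repeated-measures term in a condensed article is not itself a fault.

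What the reply does not remove is that a method is positively stated, in two sections, and does not fit the endpoint or the power calculation beside it. Nor does the article ensure that the SAP will settle the matter in time: it is due before database freeze, whereas efficacy data are to be examined at two-thirds accrual.

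**Conclusion.** The point holds as a mismatch between the named test and the endpoint. The sample size rests on a two-group comparison of delta; the analysis is called a two-way 2 × 2 ANOVA with no second factor, no chosen primary effect and a stratifier that is also the contrast.

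The numerical harm is conditional. It arises only if raw readings are analysed as arm × inflation without a patient term, and only if rho is above zero. Then, with 30 per arm and SD of delta 5 mm, interaction power is about 76%, 62% and 31% at rho 0.3, 0.5 and 0.7, against 86% for the delta comparison. At SD 4 mm it is about 93%, 85% and 60%, against 97%. The interaction test errs on the conservative side, while the arm main effect, if mistaken for the primary test, would have a type I error of about 11% at rho 0.5 and 13% at rho 0.7. At rho 0, with a patient term, or with delta as the response, the problem does not occur.

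**What to change.** In both the Sample size and Statistical analysis sections, replace the 2 × 2 ANOVA wording with one primary test:

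- Delta, defined as second minus first inflation, is compared between arms in a linear model, two-sided 5%, reported as a mean difference with a 95% confidence interval. An equivalent statement is the arm × inflation interaction in a model with a patient term.
- If adjustment is wanted, name the covariates in advance. Site and patient type (post-ACS or stable) are natural candidates and are already collected. Adjustment is optional; the unadjusted comparison is valid.
- Delete the words that make treatment group a stratifier.
- Settle this in the protocol or a signed SAP before the interim efficacy analysis, not merely before database freeze.

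The cost is wording only: no new data and no change to the target of 30 evaluable patients per group, which already gives 86% power at the larger stated SD.

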**Fig. 2 Fig2:**
[figure not shown]
Flow-chart for patients presenting with stable coronary artery disease

The study is designed to have a total duration of 23 months, with an enrollment period of approximately 20 months. Each patient will be treated with the study drug only during the in-hospital phase, for a minimum of 3 days (Day -1 to Day 1) up to a maximum of 7 days (Day -1 to Day 5). The patient will be hospitalized (as per usual clinical practice) from Day -3 to Day -1 (admission) to Day 0–5 of the study. The total number of enrolled patients will be one hundred (*N* = 100), with a projected 10% drop-out rate and 30% of negative FFR assessment (FFR > 0.80), with a final pool comprising 60 patients who will be evaluated in terms of primary and secondary endpoints. Therefore, the study enrollment will be stopped once one hundred patients are enrolled (Fig. 3).

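### The primary ST-delta is committed to single imputation with no stated scope; filling even a few values per arm distorts the test or shrinks the estimate, and the design does not need it

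*Protocol article*

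**What the plan says.** The Statistical analysis section compares the ST-segment delta between arms by a 2 × 2 ANOVA and adds: "Missing data in the primary analysis will be handled by simple imputations". It names neither the technique nor the patients, and leaves analysis detail to an SAP that is not shown.

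The design section (TAPER-S trial design, text after Fig. 2) plans 100 enrolled patients "with a projected 10% drop-out rate and 30% of negative FFR assessment (FFR > 0.80), with a final pool comprising 60 patients". The same section says that patients with FFR > 0.80 leave the study. The Sample size section states that "30 patients per group will be required to provide an 80% power" and describes the main comparison as two groups of 30.

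The delta comes from two balloon inflations within one procedure. In Table 1 the preconditioning assessment appears only at V1 (Day 0).

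**The concern.** The sentence is a stated method, so an SAP that follows it may choose which single imputation to use but not whether to impute. The method suits this endpoint poorly. A patient who never reaches the inflations has no earlier delta to carry forward, so any filled value is a mean, a draw or a constant. If only the second inflation is lost, carrying the first one forward sets the delta to zero, which presupposes no preconditioning.

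The scope is also unclear. The planned pool is already net of drop-outs and negative FFR. If drop-outs are filled, the comparison is no longer 30 against 30. If they are not, only incomplete or unreadable tracings among the 60 remain to be filled.

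A single filled value that is then analysed as observed either makes the standard error too small or pulls the arms together. The Sample size section presents the pilot as a source of interval estimates and of planning values for a larger study, and those are the outputs affected.

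**Working it through.** **Inputs.** All come from the protocol article.
- Effect: "by assuming an absolute difference (delta) of 4 mm in the change of ST-segment shift from the first to the second balloon inflation".
- SD: "The standard deviation (SD) of the primary endpoint is expected to be approximately 5 to 4 mm in each treatment group".
- Alpha: 0.05, taken as two-sided because sidedness is not stated.
- Evaluable patients: 30 per arm.
- Projected losses: 10% drop-out and 30% negative FFR.

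**1. The plan's own figures.** The evaluable pool is 100 × (1 − 0.10 − 0.30) = 60, as stated. The sample size is n = 2(1.960 + 0.842)² × SD² / 4², which gives 24.5 (25 per arm) at SD 5 and 15.7 (16 per arm) at SD 4. The stated 30 is not reproduced. It is larger than needed, which is a separate matter. With 30 per arm, power for 4 mm is 86–87% at SD 5 and 97% at SD 4.

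**2. Filling with arm means.** Let o be the observed and N the analysed number per arm. Filled means add nothing to the sum of squares but raise both the sample size and the degrees of freedom. The naive standard error is therefore the correct one multiplied by

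r = √[(o − 1)/(N − 1)] × √(o/N).

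The true type I error is P(|t| > r × t₀.₉₇₅) on 2o − 2 df, with t₀.₉₇₅ taken on 2N − 2 df.

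| Filled per arm | r | Effective critical value | Type I error |
|---|---|---|---|
| 5 of 35 | √(29/34) × √(30/35) = 0.855 | 1.995 × 0.855 = 1.706 (58 df) | 9.3% |
| 3 of 30 | √(26/29) × √(27/30) = 0.898 | 2.002 × 0.898 = 1.798 (52 df) | 7.8% |
| 1 of 30 | √(28/29) × √(29/30) = 0.966 | 2.002 × 0.966 = 1.934 (56 df) | 5.8% |

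A simulation of 40,000 trials per scenario agrees: 9.3%, 7.7% and 5.9%. It used a t test on the delta, which is equivalent to the arm-by-inflation interaction in the 2 × 2 ANOVA.

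**3. Filling with single random draws within the arm.** The same simulation gives 8.6% (5 of 35), 7.4% (3 of 30) and 5.9% (1 of 30).

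**4. Filling with the overall mean or zero.** Simulated type I error stays at about 5%, but the expected difference is multiplied by o/N:
- 5 of 35: 4 × 30/35 = 3.4 mm
- 3 of 30: 4 × 27/30 = 3.6 mm
- 1 of 30: 4 × 29/30 = 3.9 mm

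**5. Effect on the interval.** At SD 5 and 30 observed per arm, the correct 95% half-width is 2.002 × 5 × √(2/30) = 2.58 mm. After arm-mean filling to 35 it is reported as about 1.995 × 1.291 × 0.855 = 2.20 mm, and it covers the truth about 91% of the time (1 − 0.093).

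**6. Is imputation needed?** With 30 observed per arm, power exceeds 80% (step 1). If 3 of 30 per arm were lost and simply left out, simulated power at SD 5 is still 82%.

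**The case against.** The strongest reply is that the technique and the analysis populations are normally SAP matters and that the SAP is not shown. That is fair for the choice of technique, and the size of the harm does depend on it: overall-mean filling does not inflate the type I error. The reply does not reach the commitment to impute, which the article makes itself.

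A second reply is that few values would be filled. On the projected numbers the 60 are already net of drop-outs, so the natural targets are scattered incomplete tracings, and 1 of 30 per arm moves the error only to about 6%. This stands and limits the severity. It is also true that a patient with one recorded inflation has related data (simultaneous surface ECG, first-inflation ST, angina score). That supports model-based imputation as a sensitivity analysis, not a single filled value in the primary one.

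A reader might also infer that all 40 of the 100 patients expected to lack a reading would be filled, with far larger distortion. The documents do not support this. Patients with FFR > 0.80 are excluded, the plan ends "with a final pool comprising 60 patients who will be evaluated in terms of primary and secondary endpoints", and the main comparison is 30 against 30. Nowhere is it said that FFR-negative patients are imputed.

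**Conclusion.** The point holds at moderate severity. The protocol article fixes single imputation for a once-measured primary endpoint and does not say whom it covers. On the plan's own numbers it can plausibly reach only the roughly 10 drop-outs or incomplete tracings among the 60. Within-arm filling then gives a type I error of about 6% to 9% instead of 5%. Filling with the overall mean or zero shrinks a true 4 mm to between about 3.4 and 3.9 mm while leaving the test at about 5%.

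These figures assume a two-sided test, normal data, SD 5 mm for the simulated error rates, values missing completely at random, and equal numbers missing in each arm. The zero-filling error rate was simulated with both arm means at zero. If missingness depended on arm or on severity of ischaemia, neither these figures nor an observed-data analysis would be protected from bias, which is why a sensitivity analysis is needed.

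**What to change.** Replace the imputation sentence with:

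> The primary analysis uses all randomised patients with both inflations recorded, analysed as randomised, without imputation. Patients with FFR > 0.80 have no endpoint and are not imputed. Missing readings are reported by arm.

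Add one sensitivity analysis by simple multiple imputation, restricted to patients with FFR ≤ 0.80 who lack a reading. Use a small model, for example arm, site and first-inflation ST where recorded, since only about 60 to 70 patients are involved. Fix both in SAP version 1.0, before the database freeze.

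The cost is one sentence, one extra analysis and slightly wider confidence intervals (in the drop-out case at SD 5, a half-width of about 2.6 mm instead of an understated 2.2 mm). Enrolment does not change.
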